##### Exploring mediation and moderation

To explore pathways by which the *Suubi+Adherence* intervention effects change in outcomes, secondary analyses will investigate whether the potential mechanisms of change listed in Table 1 mediate the relationships between intervention group assignment and sexual risk, HIV viral suppression, STI, mental health outcomes, and neurological functioning, and whether geographic location, exposure to other HIV/STI prevention programs, household income and asset accumulation moderate those associations. Mediation and moderation will be assessed using the causal inference-based approach of Valeri and VanderWeele, which yields optimal estimates of indirect effects in the presence of non-continuous (e.g. binary) outcomes and moderator-mediator interactions [195]. M*plus* will be used to fit mediation models because it can adjust standard errors for clustering of participants within clinics [196].

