To elucidate the long-term effects of the *Suubi+Adherence* intervention on potential mechanisms of change, including: a) economic stability, sexual risk-taking behavior, adherence self-efficacy; b) cognitive functioning (global cognition as well as cognitive domains of memory, and executive functioning) using cognitive tests previously validated in Uganda among YLHIV [19, 20]; c) mental health functioning (hopelessness, depression, self-efficacy); and d) young adult transitions and social support.

### Aim 3

To qualitatively examine– prospectively and retrospectively–: a) multi-level factors affecting participants’ maintenance of intervention benefits since *Suubi+Adherence* intervention initiation (prospectively); and b) participants’ experiences with the intervention (retrospectively), including multi-level factors that may have influenced their engagement with the program, as well as their decision-making in regard to ART adherence.

### Aim 4

To examine the long-term cost-effectiveness of the *Suubi+Adherence* intervention.

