In another analysis [5], we assessed whether missing ART medication doses among our participants was significantly associated with individual- and community-level indicators of inequities, including economic (availability of household assets, employment and food security), social support, and structural inequities (participants’ access and proximity to community resources, including schools, and health clinics). These are important questions as they relate to social transitions YLHIV go through. Greater asset ownership (a proxy for financial stability) was associated with greater odds of self-reported adherence (OR 1.69, 95% CI: 1.00–2.85). Also, we found that distance to the nearest health clinic impacts youth’s adherence to an ARV, with youth who reported living nearer to a clinic more likely to report optimal adherence (OR 1.49, 95% CI: 0.92–2.40). Moreover, we found that youth with greater economic advantage in assets-ownership and financial savings report higher odds of adherence (OR 1.70, 95% CI: 1.07–2.70) [5]. Specific to financial savings, the mean savings for participants in the intervention arm increased from USD equivalent of $2.15 at baseline to $19.34 at 24-months, while the control arm participants’ mean savings increased from $1.78 to $4.44 over the same time period.

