**Table 2 Tab2:** Suubi+Adherence-R2 Study Measures

Variable	Measurement	Reliability	Timepoint
Demographics (Respondent: Adolescent Participant)			
Age; sex (assigned at birth), orphan status (single vs. double); socioeconomic status; family composition/structure; caregiver educational level	Socio-demographic questionnaire	n/a	^a^T1-RC, 12, 24, 36, 48
Moderators (Respondent: Adolescent Participant)			
Rural/urban/semi-urban; exposure to outside HIV/STI-related programs; economic/household income; asset accumulation			^a^T1-RC, 12, 24, 36, 48
Potential Mechanisms of Change (Respondent: Adolescent Participant)			
Self-efficacy	Adapted Tennessee Self-Concept Scale [147] (TSC-2) (*pretested in Suubi Studies*)	0.81	^a^T1-RC, 12, 24, 36, 48
Education plans/aspirations	Adapted Monitoring the Future Survey [148]	n/a	^a^T1-RC, 12, 24, 36, 48
Motivation to participate	Questions tested in previous studies [103, 124, 149, 150]	n/a	^a^T1-RC, 12, 24, 36, 48
Family Support	Social Support Behaviors Scale (SS-B) [151]Family Cohesion Scale [152], Krauss Interview [153]Parent Child Relationship Inventory (PCRI) [154]	0.77 0.69 0.91	^a^T1-RC, 12, 24, 36, 48
Family Stability	Socio-demographic questionnaire	n/a	^a^T1-RC, 12, 24, 36, 48
Hopelessness	Beck Hopelessness Scale [152]	0.79	^a^T1-RC, 12, 24, 36, 48
Self-esteem	Rosenberg Self-Esteem Scale [155]	0.77-0.88	^a^T1-RC, 12, 24, 36, 48
Condom Negotiation Self-Efficacy	Condom negotiation self-efficacy scale [156]	0.80	^a^T1-RC, 12, 24, 36, 48
Sexual Communication Skills	Sexual Communication Scale [157]	0.80	^a^T1-RC, 12, 24, 36, 48
Transitions (education, employment, residential independence, prosocial transition, relationship/marital status, pregnancy/parenthood	Demographics, MTF, Work history interview, Relationship assessment scale, Adolescent Sexual Behavior Assessment (ASBA), additional prosocial activities		^a^T1-RC, 12, 24, 36, 48
Social Support	Multidimensional scale of perceived social support MSPSS [158]	0.84	^a^T1-RC, 12, 24, 36, 48
Access to services	RBA Services [159], Treatment Services Review (TSR) teen and adult versions [160–162]	.66-.83	^a^T1-RC, 12, 24, 36, 48
Cost of staff time, supplies, overhead for IDAs	Project records; Admin. Review	n/a	ongoing
Substance misuse	Questions adapted from PhenX Toolkit [163], Alcohol, Smoking, and Substance Involvement Screening Test [164], DISC-IV modules, CIDI modules	n/a; 0.58-0.90	^a^T1-RC, 12, 24, 36, 48

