**Primary Outcomes (Respondent: Adolescent Participant)**			
Viral load/Virologic Suppression*	Biomedical data: Viral load*	n/a	^a^T1-RC, 12, 24, 36, 48
Secondary Outcomes (Respondent: Adolescent Participant)			
Adherence	Self-Report Questionnaire, Pill Counts, adherence self-efficacy [172]		^a^T1-RC, 12, 24, 36, 48
Financial/economic stability (savings and asset accumulation)	Bank statements, MIS IDA, and American Dream Policy Demonstration [173]	n/a	^a^T1-RC, 12, 24, 36, 48
Sexual risk taking behavior:	Time-line Follow Back (TFLB) [174, 175] Adapted Youth Aids Prevention Project (used in Suubi & CHAMP) [176]	n/a	^a^T1-RC, 12, 24, 36, 48
Mental Health Functioning	Center for Epidemiological Studies-Depression Scale (CES-D) [177]	0.65	^a^T1-RC, 12, 24, 36, 48
STIs	Biomedical data: Gonorrhea, Chlamydia, Trichomonas	n/a	^a^T1-RC, 12, 24, 36, 48

^a^T1-RC – Time 1 at reconsenting.

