##### Exploring trajectories of change over the full developmental period captured by the Suubi+Adherence project

Moderator, mediator, and sexual behavior and mental health outcome data will be available at 10 time points from the start of the original *Suubi+Adherence* through the end of the *Suubi+Adherence-R2* study. We will initially explore trajectories of these variables by generating spaghetti plots of participants’ individual trajectories with study arm averages overlaid to visualize group average (i.e., mean) levels of change and inter-participant variability. Next, we will fit mixed effects growth models to learn whether change over time can be quantified using low-dimensional parametric functions (e.g., linear, quadratic) of explanatory variables. Finally, we will employ the highly flexible time-varying effect model (TVEM) to go beyond simple parametric functions to elucidate the form of variables’ changes over time. TVEM allows the effects of covariates on outcome trends to vary over time non-parametrically [197]. TVEMs will be fitted using the %weightedTVEM SAS macro from the Penn State Methodology Center, a leader in developing longitudinal analysis methods and software. The %weightedTVEM [198] macro includes support for clustered data, enabling us to account for clustering of participants within clinics. Moderation by intervention group will be featured in all trajectory analyses to estimate separate slopes or curves for control and *Suubi+Adherence* treatment groups.

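### Household income and asset accumulation are planned as moderators but, as scheduled, are measured years after an intervention meant to raise them; the exploratory moderation analyses should use the pre-randomisation values.

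*Protocol article*

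**What the plan says.** The section Exploring mediation and moderation asks whether mechanisms of change mediate the link between arm and several outcomes, and "whether geographic location, exposure to other HIV/STI prevention programs, household income and asset accumulation moderate those associations". It gives no time point for the moderators.

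The Moderators block of Table 2 reads "Rural/urban/semi-urban; exposure to outside HIV/STI-related programs; economic/household income; asset accumulation", with measurement at re-consenting and 12, 24, 36 and 48 months later. The section Time points used in inferential analyses restricts all primary and most secondary inferential analyses to Round 2 data. The one exception it names is the developmental trajectory analyses.

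Table 2 also lists, as a secondary outcome, "Financial/economic stability (savings and asset accumulation". H2(c) predicts higher economic stability in the intervention arm. Aim 2 speaks of "potential mechanisms of change, including: a) economic stability, sexual risk-taking behavior, adherence self-efficacy". For the mediators, the pathway section sends the reader to Table 1.

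**The concern.** A moderator should be fixed before the intervention can act on it. If the arm changes it, intervention and control participants at the same later level of assets are no longer comparable: some of the former reached that level through the programme, the latter without it. A contrast within such strata is not protected by the randomisation of clinics. If assets also lie on the causal path, conditioning on them removes part of the effect under study.

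What is at stake is the answer to whether the programme works differently for poorer and better-off youth. Readers may use that answer to target the intervention, even though the analysis is labelled exploratory.

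A second, smaller matter is the mediator list. The study rests on asset theory, yet the table block that appears to define the mediators has no row for savings, assets or economic stability.

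**Working it through.** The plan states no figure for this analysis, so there is none to reproduce. The check compares sections and then uses a labelled illustration.

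**1. When the moderators are measured.** The first Table 2 time point is re-consenting, which the retention section places at wave 6 in 2020. The original study ran from 2012 to 2018. With the Round 2 restriction, and with moderation not among the exceptions, the values used would be post-intervention.

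**2. Whether the intervention affects them.** The overview of the original study says the intervention was intended to stabilise families so that they have enough income. For savings there are data. The results section reports that "the mean savings for participants in the intervention arm increased from USD equivalent of $2.15 at baseline to $19.34 at 24-months", against $1.78 to $4.44 in the control arm.
- Change, intervention: 19.34 − 2.15 = $17.19
- Change, control: 4.44 − 1.78 = $2.66
- Difference in change: 17.19 − 2.66 = $14.53
- Ratio of 24-month means: 19.34 / 4.44 = 4.4

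For household income no arm difference is reported.

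**3. Whether assets relate to the outcome.** The same section gives odds ratios for self-reported adherence of 1.69 (1.00–2.85) for asset ownership and 1.70 (1.07–2.70) for assets and savings. These do not concern viral suppression.

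**4. What conditioning can do (illustration; every parameter is assumed).** Let A be arm, U an unmeasured cause, and B baseline assets with variance 1 and covariance 0.5 with U. The outcome is Y = 0.30A + cU + error, with no true moderation. Later assets S equal B in the control arm and 0.5 + kB in the intervention arm. Take c = 0, 0.3, 0.6.

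- *Shift only (k = 1).* The within-arm slope of Y on S is 0.5c in both arms. The arm coefficient is 0.30 − 0.5 × 0.5c = 0.30 − 0.25c, giving 0.30, 0.225, 0.15. The interaction is 0.
- *Shift and doubled spread (k = 2).* The slopes are 0.5c (control) and 0.25c (intervention), so the interaction is −0.25c: 0, −0.075, −0.15. At the overall mean of S (0.25) the arm effect is 0.30 + 0.25c(0.25 − 0.5) − 0.5c(0.25) = 0.30 − 0.1875c, giving 0.30, 0.24, 0.19.
- *Half the effect through assets (k = 1).* With Y = 0.15A + 0.3S + cU + error, the total effect is 0.15 + 0.3 × 0.5 = 0.30. Given S, the arm coefficient is 0.30 − 0.5(0.3 + 0.5c) = 0.15 − 0.25c, giving 0.15, 0.075, 0.00. The fall from 0.30 to 0.15 is the mediated path; only the further fall is confounding.
- *Baseline B as moderator in the first two cases.* The arm effect is 0.30 and the interaction 0 throughout.

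A simulation of 1,000,000 records per setting agrees with these values to within 0.003.

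**5. Whether pre-intervention values exist.** The overview of the original study places baseline assessment before clinics were assigned. The trajectory section says "Moderator, mediator, and sexual behavior and mental health outcome data will be available at 10 time points", counted from the start of that study.

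**6. The mediator list.** Table 1 holds retention rates. The mechanisms block is in Table 2 and has no economic stability, savings or asset row. Those items appear only under moderators and secondary outcomes.

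**The case against.** **Timing is inferred.** The pathway section names no wave, Table 2 is a collection schedule, and the Round 2 rule covers most rather than all secondary analyses. Its reason, to avoid reusing outcomes already examined, does not bar a baseline moderator. This stands as a limit on certainty. But the only exception named is a different analysis, so a reader who follows the text arrives at post-intervention values.

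**Roles.** A reader might infer that asset accumulation has three incompatible roles. It does not: a mediator must be affected by arm, so being an H2(c) outcome and a mechanism is coherent. Only the moderator role conflicts.

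**Mediators.** A reader might also infer that the study will not test its own economic pathway. The documents do not support that. The table reference is broken, Aim 2 names economic stability first among the mechanisms, and other Aim 2 mechanisms, such as adherence self-efficacy and depression, also sit under secondary outcomes. The mechanisms block even includes a row on staff and supply costs, so it cannot be a literal mediator list. What stands is a wrong cross-reference and a list that needs completing.

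**Size.** The 4.4-fold savings ratio has no standard deviation, refers to 24 months, and is not a measure of bias. A shift in the arm main effect is not a shift in the interaction; with equal slopes in both arms the interaction stays at zero. This stands in full.

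**Conclusion.** The point holds for the exploratory moderation analyses. As the sections combine, income and assets would be post-intervention moderators, and the plan itself treats asset accumulation as something the intervention raises. Arm effects within strata can be distorted when the moderator is affected by arm and either shares causes with the outcome or lies on the pathway. The interaction can be distorted if the intervention also changes the spread of assets or their relation to the outcome.

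The size is unknown. The illustrated range, from no distortion to half of an assumed effect of 0.30 (0.30 down to 0.15), rests wholly on assumed inputs and a linear outcome, whereas viral suppression is binary. The evidence that the arm affects the moderator is direct for savings and only intended for income. It would go too far to say that the pathway analyses as a whole are biased. H1(a) and H2(a)-(g) do not condition on these variables and are untouched.

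**What to change.** 1. In Exploring mediation and moderation, state that household income and asset accumulation, when used as moderators, are the wave-1 values collected before clinics were randomised.
2. In Time points used in inferential analyses, name this as an explicit exception to the Round 2 restriction. Baseline covariates are not reused outcomes, so the reason for the restriction is respected.
3. Correct the mediator reference from Table 1 to Table 2, and add economic stability (savings and assets) to the mechanisms listed there, in line with Aim 2. It can remain the H2(c) outcome as well.

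The cost is a few sentences and one table row. The trajectory section indicates that the data exist, so no new collection is needed and the primary analyses do not change.

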##### Exploring trajectories of change over the full developmental period captured by the Suubi+Adherence project

Moderator, mediator, and sexual behavior and mental health outcome data will be available at 10 time points from the start of the original *Suubi+Adherence* through the end of the *Suubi+Adherence-R2* study. We will initially explore trajectories of these variables by generating spaghetti plots of participants’ individual trajectories with study arm averages overlaid to visualize group average (i.e., mean) levels of change and inter-participant variability. Next, we will fit mixed effects growth models to learn whether change over time can be quantified using low-dimensional parametric functions (e.g., linear, quadratic) of explanatory variables. Finally, we will employ the highly flexible time-varying effect model (TVEM) to go beyond simple parametric functions to elucidate the form of variables’ changes over time. TVEM allows the effects of covariates on outcome trends to vary over time non-parametrically [197]. TVEMs will be fitted using the %weightedTVEM SAS macro from the Penn State Methodology Center, a leader in developing longitudinal analysis methods and software. The %weightedTVEM [198] macro includes support for clustered data, enabling us to account for clustering of participants within clinics. Moderation by intervention group will be featured in all trajectory analyses to estimate separate slopes or curves for control and *Suubi+Adherence* treatment groups.

##### Sex as a biological variable

In line with recent NIH guidelines on exploring sex differences in effects, all previously described inferential analyses will be repeated with models extended to include sex assigned at birth as a moderator to examine whether effects vary by participant sex.

#### Statistical Power Analysis for Aims 1 and 2

We used NCSS PASS [199] to compute minimum detectable effect size estimates for the primary hypotheses H1(a) and H2(a)-H2(g) proposed to fulfil Specific Aims 1 and 2, respectively. For all power analyses we assume power=.80 and 5 repeated assessments from N=450 participants conservatively assuming 20% attrition. For H1(a), based on our current *Suubi+Adherence* project’s data we further assumed a control proportion of 65% virally suppressed, α=.05, and an intraclass correlation (ICC) of .032 at the clinic level and .819 at the person level. Under these assumptions, the minimum detectable raw proportion difference is 13%, which corresponds to an odds ratio (OR) of 1.91 and a standardized effect estimate *h*=.29, which is between a small (*h*=.20) and medium (*h*=.50) effect size [200] The minimum detectable OR of 1.91 is less than ORs obtained in the *Suubi+Adherence* study [6] ensuring that we will have sufficient power to detect similar or slightly smaller effects in the project period. For H2(a)-H2(g), we computed the minimum detectable standardized mean difference *d* using the same inputs as listed above, α=.007, and a range of ICCs from .003 to .542 for change mechanisms based on data from the *Suubi+Adherence* study. Under these conditions *d* ranged from .10 to .13, which are small standardized effect sizes [201]. Taken collectively, our study will have sufficient power to detect small to small-medium effects across a wide variety of conditions.

#### Qualitative data analysis for Aim 3

All interviews will be transcribed (and translated to English where necessary). Transcripts will be compared with digital records to ensure transcription accuracy. All transcripts will be uploaded to QSR NVivo12 analytic software for analysis. Interview transcripts will be reviewed by the research team to develop a broad understanding of content as it relates to the project’s aims and to identify topics of discussion. During this step, as well as during subsequent steps, analytic memos will be written to further develop categories, themes, and subthemes, and to integrate the ideas that emerge from the data [202–204]. Using analytic induction techniques [205], transcripts will be read multiple times for initial coding by the research team. For initial coding, randomly selected 10 interview transcripts will be read multiple times and independently coded by the project investigators using a priori (i.e., from the interview guide) or emergent themes (also known as open coding) [202, 206]. Broader themes/categories will be broken down into smaller, more specific units until no further subcategory is necessary. For example, potential themes and subthemes for barriers and facilitators to adherence may include: at the individual-level (e.g., motivation, readiness to change, savings, household income), family-level (e.g., support); and macro-level (e.g., cultural norms, stigma). These findings will also further contextualize the mediators and moderators and may identify additional variables to be considered as part of mechanisms of change.

The codes and definition boundaries of specific codes (inclusion and exclusion criteria for assigning a specific code) [207] will be discussed during team meetings to create the final list of codes (known as codebook) in NVivo. Each text will be independently coded by two investigators using the codebook. Inter-coder reliability will be established. A level of agreement from 66 to 97% depending on level of coding (general, intermediate, specific), indicates good reliability in qualitative research [203]. Disagreements will be resolved through discussion during team meetings. The secondary analysis will focus on comparing and contrasting themes and categories within and across groups to identify similarities and differences). To further ensure rigor, study results will be presented to study participants, enabling them to provide comments and suggest modifications or additional avenues of investigation when possible (member checking) [204, 208]. An audit trail [204, 208] of data as well as memos and minutes of team meetings will be kept throughout the study.

#### Cost-effectiveness (CE) analysis for Aim 4

CE analyses measure the cost of an intervention relative to other means of achieving the same desirable outcome. Following standard practice, we will measure costs on a per person basis. The costs of the intervention include all costs for running program activities. Research costs will be excluded. Data on the costs of other program elements will be drawn from project administrative records. Outcome analyses described above will be used to assess the extent to which *the intervention*, in the long-run, affected particular outcomes. The per-person costs of *the intervention* will then be divided by the relevant effect sizes to estimate CE ratios. For example, suppose that, over the 10-year period, *the intervention* costs per child were respectively $500 and $750 and, on average, increased years of schooling completed by one year and two years. The CE ratios described above (section C.2.3) will, like the effect sizes from which they derive, be point estimates. Confidence intervals based solely on effect size confidence intervals ignore the cost portion of CE. But cost estimates are also only point estimates on a per person basis. We will calculate confidence intervals using two methods [209, 210]: Monte Carlo [211] and bootstrap [211]. Finally, for some outcomes, such as increases in education and health, we will be able to compare the CE of *the intervention* to other interventions in developing country settings [212–218].

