### Sample Tracking, Retention and Attrition

The *Suubi+Adherence* study (2012-2018) had an attrition rate of 6.6%, leaving a total study sample of 656 – by study end (December 2018). These numbers reflect: a) the study being implemented in a stable region with low geographical moves; b) trust of the study team by the community members. This trust has been built and/nurtured over a 15+ year period that [name] (Lead PI) and his colleagues have been engaged in the greater Masaka region and the surrounding districts; c) Washington University has a fully-fledged field office (ICHAD) in the Masaka region allowing for easy engagement between the study team and the local collaborators; and d) the study team has a well-established tracking system implemented by ICHAD resulting in very low attrition rates—as reflected in Table 1 below, detailing actual retention rates from the *Suubi+Adherence* original study.

**Table 1 Tab1:** Suubi+Adherence Retention rates: (2012-2018) [48, 49, 135]

Baseline/Wave 1	Wave 2	Wave 3	Wave 4	Wave 5
*N*=702	*N*=670, retention rate=95.4% (lost to follow-up *n*=32)	*N*=663, retention rate=94.4% (lost to follow-up *n*=39)	*N*=662, retention rate=94.3% (lost to follow-up *n*=40)	*N*=656, retention rate=93.4% (lost to follow-up *n*=46)

During re-consenting, we will ask participants to update their future contact information with updated telephone number(s) (if they have one: 95% of participants reported having access to a phone in the household), and an updated list of the names, and contact information of three people who will always know how to reach them. Participants will be reminded that if we contact the people listed, we will not discuss any details about them or their study participation. Like we have done in the past, we will use these records solely to help track their location and only if we have lost contact. We have effectively used these procedures in our previous research studies, resulting in very low attrition rates. Thus, we conservatively expect to re-consent at least 80% of the 702 participants (N=562) for the Suubi+*Adherence-R2* study. We expect attrition from reconsented cohort (wave 6, in 2020) to the end of the follow-up period (wave 10 in 2025) to be no more than 20%. (See Table 1 above).

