#### Time points used in inferential analyses

To maximize rigor, to assure alignment of cognitive functioning data (only measured in the *Suubi+Adherence-R2 study*) and our remaining outcomes, and to avoid reuse of *Suubi+Adherence* outcomes (already examined for shorter-term intervention efficacy) that would bias tests of longer-term intervention efficacy, all primary inferential analyses and most of the secondary inferential analyses listed will use only Suubi+*Adherence-R2* data. The exception is longitudinal developmental trajectory analyses to explore associations between changes in time-varying covariates and mechanisms of change with outcomes measured across both *Suubi+Adherence* and *Suubi+Adherence-R2*.

#### Primary Analyses for Aim 1

We hypothesize that participants in the *Suubi+Adherence* intervention group will exhibit a higher odds of HIV viral suppression relative to participants in the bolstered standard of care (BSOC) control condition (H1a) during Suubi+*Adherence-R2*. To test H1a, we will fit a three-level generalized linear mixed model (GLMM) with fixed effects for study arm, time, and their interaction. We will use random intercepts for Clinic ID to account for clustering of persons within clinics and include random intercepts, random slopes, and their covariance for person ID to account for clustering of repeated measurements within persons. Reflecting the binary HIV viral suppression outcome, a binomial distribution and logit link will be used. To test H1a we will perform a time-averaged comparison of repeatedly measured observations across study arms to examine intervention effects over the duration of the study period. Alpha will be set at .05 for this planned comparison.

#### Secondary Exploratory Analyses for Aim 1

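### The minimum detectable odds ratio of 1.91 for H1a is population-averaged, so it is not the benchmark for the person-conditional odds ratio that the planned GLMM yields

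*Protocol article*

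**What the plan says.** The section Statistical Power Analysis for Aims 1 and 2 sets the common inputs: "For all power analyses we assume power=.80 and 5 repeated assessments from N=450 participants conservatively assuming 20% attrition". For H1a it takes 65% suppression in the control arm and an alpha of .05. Its clustering inputs are "an intraclass correlation (ICC) of .032 at the clinic level and .819 at the person level". It does not say whether these ICCs are on the latent logit scale or are correlations of the observed binary outcome. The result is that "the minimum detectable raw proportion difference is 13%, which corresponds to an odds ratio (OR) of 1.91", with a standardised effect h of .29. The section then calls 1.91 the minimum detectable OR, notes that it lies below the ORs obtained in the original study (source 6), and concludes that power for similar or slightly smaller effects is assured.

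The section Primary Analyses for Aim 1 specifies the H1a test: a three-level generalised linear mixed model with arm, time and their interaction, and a random clinic intercept. For the person level it will "include random intercepts, random slopes, and their covariance for person ID". For the outcome, "a binomial distribution and logit link will be used". The hypothesis is stated as higher odds of suppression and is tested by a time-averaged comparison between arms. The scale on which that comparison will be reported is not given.

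**The concern.** An odds ratio is not collapsible. In a logistic model with large between-person variance, the odds ratio conditional on the person is further from 1 than the odds ratio formed from the two arms' overall proportions, although both describe the same data. The power section works with overall proportions; the H1a model yields the conditional quantity. The article prints one odds ratio and does not say which kind it is.

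Two readings are at stake. First, a model odds ratio near 2 could be taken as close to the smallest effect that the study was sized to find, although it stands for a rise of only a few points; a model odds ratio near 5 could be taken as far above plan, although on the latent-scale reading it is the planned 13 points. Second, the assurance about power rests on placing 1.91 beside earlier odds ratios, which is valid only if both are on the same scale.

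**Working it through.** **Inputs.** 450 people, 5 assessments, control proportion .65, alpha .05 (taken as two-sided), ICCs .032 (clinic) and .819 (person), all from the power section. The 450 is 80% of 562 (562 x .80 = 449.6); the section Sample Tracking, Retention and Attrition gives the 562: "we conservatively expect to re-consent at least 80% of the 702 participants (N=562"). The 39 clinics (19 control, 20 intervention) come from the overview of the original study.

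**Step 1: reproduce the printed figure.**
- Design effect = 1 + 4(.819) + 5(450/39 - 1)(.032) = 5.96.
- Effective n = 2250/5.96 = 377, or 188.7 per arm.
- Pooled two-proportion test at .65 v .78: z = (.13 - 1.96 x .0465)/.0460 = .846, so power = .80 (unpooled, .81).
- Minimum detectable difference: 12.98 points pooled, 12.89 unpooled.
- OR = (.78/.22)/(.65/.35) = 1.909; h = .290.

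All three printed figures reproduce. The 1.91 is formed directly from two overall proportions and is therefore population-averaged.

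**Step 2: translate to the model scale.** Take logit P = a + b(arm) + random effect, with a normal random effect of total variance V. Integrate over it, choose a so that control suppression is 65%, and solve for b.

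| Reading of .819 | V | Conditional OR for 65% v 78% | Suppression at conditional OR 1.91 | Marginal OR there |
|---|---|---|---|---|
| Latent-scale ICC | (.819/.181) x pi²/3 = 14.9 | 5.2 | 70.5% | 1.28 |
| Latent, with .819 and .032 as separate shares | (.851/.149) x pi²/3 = 18.8 | 6.1 | 70.0% | 1.25 |
| Observed-scale correlation | 77.7 | about 32 | 67.6% | 1.12 |

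**Step 3: power if 1.91 is read as the model's OR.**
- Latent scale: 20% with the design effect of 5.96. With the observed correlations that this reading implies (.617 person, .0195 clinic), the design effect is 4.49 and power is 26%. The separate-shares variant gives 18-21%.
- Observed scale: 7.8%.
- Simulation of a three-level random-intercept logistic model (39 clinics, 450 people, 5 waves, maximum likelihood, likelihood-ratio test, 300 runs per scenario): 26% latent and 8.7% observed. The observed-scale run used rounded variances of 80 (person) and 3 (clinic). Rejection under the null was 3.7% and 4.3%.

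**Step 4: power of the model at the stated 13 points.** By design effect: 80% (5.96) to 90% (4.49). In the same simulations: 87% latent, 80% observed. A separate simulation of the latent reading gave 91% here, and 26% at a conditional OR of 1.91. The coefficient and its standard error grow together, so using the mixed model does not in itself cost power.

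**Step 5: the comparison with earlier results.** The article does not give the earlier ORs or their scale. In its progress section on the original study, the only intervention effect reported from source 6 is a hazard ratio of 1.56. Multilevel logistic regressions are mentioned there for the cost-effectiveness work. If the earlier ORs were person-conditional with similar between-person variance, the matching benchmark would be about 5-6 or about 32. Any earlier OR between 1.91 and that value would pass the printed comparison while being smaller than the 13 points.

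**The case against.** The strongest reply is that nothing printed is numerically false. The power section attaches 80% power to a raw difference from 65%, says that this corresponds to 1.91, and never calls 1.91 a model coefficient. The 13 points and h stand beside it, so a careful reader has the right benchmark. All of this stands. A reader might infer from the 8-26% that the primary analysis is underpowered, or that the sample size arithmetic is wrong. The documents support neither: those percentages belong to a smaller effect (65% to about 68-70%), and at the effect the plan states the mixed-model test keeps its power.

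It is also fair to say that the reporting scale of the H1a contrast is normally left to an analysis plan, which is not shown, and that the earlier ORs may be close to population-averaged, for instance if they came from models with clinic effects only. The comparison would then be reasonable. But the article does not say so. It also does more than convert a proportion difference in passing: it names 1.91 as the minimum detectable OR of the primary hypothesis and draws an assurance of power from it. That step needs a scale, and none is given.

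**Conclusion.** The point holds as one of scale and use. The minimum detectable difference of 13 points and its 80% power are sound. The odds ratio of 1.91 is population-averaged and should not serve as the benchmark for the H1a model's odds ratio, where 13 points is about 5.2 (latent-scale ICC; 6.1 in the separate-shares variant) or about 32 (observed-scale). The claim that power is assured because earlier odds ratios exceed 1.91 is not supported as written.

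This rests on a two-sided test, near-equal clinic sizes, normal random effects and a random-intercept model. The planned random slopes were not included because no slope variance is given, so the 80-90% and 8-26% figures are approximate for the model that will be fitted. The spread from 5.2 to 32 arises from the unstated ICC scale; the conclusion is the same at either end.

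**What to change.** In Statistical Power Analysis for Aims 1 and 2:
- Keep 13 points (65% v 78%) as the minimum detectable effect.
- Label 1.91 as a population-averaged odds ratio.
- State the scale of the ICCs, and give the conditional odds ratio that matches 13 points on it (about 5.2 latent, about 32 observed).
- Do not print in its place the conditional odds ratio at which a simulated model reaches 80% power. On the latent reading, with a standard error of about .495, that is exp(2.80 x .495) = about 4.0. It moves 65% to 76.2%, about 11 points, so it is a different effect.
- Compare with the earlier results on one scale, or as differences in proportions. Otherwise drop the sentence that claims assured power.

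In Primary Analyses for Aim 1, report the time-averaged H1a contrast also as a standardised risk difference and marginal odds ratio with confidence intervals, by integrating the fitted model over its random effects and averaging over waves. The result can then be read against the 13 points.

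The cost is some rewording and one post-estimation step from the model already planned, with no new data or participants. The drawback is a model-scale odds ratio that looks less favourable than 1.91.
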